In summary, preliminary investigations of ACT in the treatment of adult anxiety have produced promising results. Other studies have also supported the use of mindfulness - one of the six ACT core processes - in the treatment of childhood anxiety, which suggest that approaches employed within ACT appear to be suitable for child populations. To the best of our knowledge, this will be the first randomized controlled trial to examine the effectiveness of ACT in young people with a diagnosed anxiety disorder. Given the popularity and use of ACT in clinical practice [10], it is imperative that this form of intervention be empirically evaluated for its efficacy. Thus, the aim of this research is to examine the effectiveness of a manualized ACT group-therapy program in the treatment of anxiety disorders among children and adolescents. It is hypothesized that ACT will be at least as effective in the treatment of anxiety disorders in these populations relative to a manualized CBT group-therapy program, and that ACT will be more effective in the treatment of anxiety disorders in this population relative to the control condition at both immediate post-treatment and at three-month follow-up on outcome measures. The secondary aim of the trial concerns the adolescent participants and is to identify the mechanisms of change surrounding the intervention that are critical to changes in outcome measures. It is hypothesized that these will include decreased experiential avoidance and cognitive fusion, as well as increased emotional awareness, acceptance and valued living.

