### Participants

Participants will be approximately 150 children (90 younger and 60 older children) aged 7 to 17 years with a primary diagnosis of a Diagnostic and Statistical Manual of Mental Disorders (DSM-IV) anxiety disorder. The participants will be age-classified as ‘children’, aged 7 to 11 years, and ‘adolescents’, aged 12 to 17 years. Twelve years of age was determined as the cut-off point to be consistent with other research involving ACT as a treatment for problems among adolescents [20].

Participants will be recruited via referrals to the Department of Psychological Medicine, The Children’s Hospital at Westmead (CHW), Sydney, NSW, Australia. Referrals will be accepted from anyone, including health professionals (general practitioners, psychologists, pediatricians), educational providers, and self-referrals. Written informed consent will be obtained from the parent or caregiver of the children and from the child/adolescent. Ethical approval was obtained for this study from the Human Research Ethics Committee at CHW and at The University of Newcastle.

The researchers predict that the majority of referrals will come from school counselors, followed by word of mouth, then via parents’ referral through the CHW intake phone line. In terms of proportions, it is expected that 60% to 70% of referrals will come from school counselors. On the basis of recruitment efforts to date and requests to intake phone line, the researchers consider that the anticipated sample will be achieved.

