*Valued Living Questionnaire (VLQ)*[59]*.* The VLQ measures valued living or the degree to which an individual accesses their chosen values in everyday life [59]. The VLQ is comprised of two 10-item scales, where participants rate the importance of different domains of life - family, intimate relationships, parenting, friendship, work, education, recreation, spirituality, citizenship and physical self-care - and subsequently rate the consistency with which they have acted in accordance with their values in the past week [59]. Wilson *et al*. [59] found the VLQ to demonstrate adequate-to-good internal consistency across domains.

For the secondary aim of the trial, relating to the mechanisms for change, process outcome measures have been developed for adolescents only and have been selected in accordance with the domains hypothesized to be associated with treatment efficacy in line with results of previous research (described above). As such, primary process outcome measures include experiential avoidance, cognitive fusion, acceptance and valued living (Table 2).

**Table 2 T2:** Primary outcome measures as they relate to the mechanism of change aim

**Mechanisms of change outcome measures**	**Assessment tool/measured factor**
Experiential avoidance	AFQ-Y, PANAS-X, TAS-20
Cognitive fusion	AFQ-Y
Acceptance	CAMM-20
Valued living	VLQ

AFQ-Y, Avoidance and Fusion Questionnaire - Youth; CAMM-20, Child and Adolescent Mindfulness Measure; PANAS-X, Positive and Negative Affect Schedule; TAS-20, Toronto Alexithymia Scale; VLQ, Valued Living Questionnaire.

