### Statistical analysis

Data coding and analysis will be conducted using the IBM SPSS Statistics v.21 software program. Primary outcome measures will be examined both with intention-to-treat analyses and analyses conducted on treatment completers. For the efficacy hypotheses, paired t-tests and linear mixed models will be used to investigate changes in pre versus post primary and secondary outcome measures. Statistical significance will be considered as *P <*0.05. The mixed model approach has been selected as it allows for inter-participant and intra-participant variance as well as the inclusion of participants with missing data, whilst maintaining power.

In accordance with the protocol of Forman *et al*. [70], mechanism of change hypotheses will be examined using correlation and independent t-tests to determine which variables to include in a multivariate analysis of variance. Post-hoc multiple comparisons (for example, Bonferroni correction) will be performed to determine where significant differences lie. Multivariate regression examining factors related to treatment success will also be employed and will include examining any demographic (such as age, gender, family functioning) and clinical (such as pre-scores, psychological flexibility) factors that might be related to outcomes. Mediational analysis, a regression-based approach, will be used to test hypotheses about the mechanisms behind outcome, as this is a powerful way of determining mechanisms by which an effect operates rather than the existence of an effect [73]. It allows for more than one mediator and adjusts all paths for the potential influence of covariates not proposed to be mediators in the model. Receiver operating curve plots of the true positive and false positive rate for different possible cut-points of the regression test will be conducted because receiver operating curves convey information relating to the trade-off between sensitivity and specificity, and maximize predictive value. The coordinates of the receiver operating curve will be used to determine the optimal cut-point for the test. The full information maximum likelihood method will be used to deal with missing data.

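### Process variables are screened into the MANOVA on the same adolescents' data, although they are already fixed in advance; where arm t-tests gate entry, the MANOVA's error rate is well above 5%

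*Protocol article*

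**What the plan says.** The Statistical analysis section of the protocol article states that "mechanism of change hypotheses will be examined using correlation and independent t-tests to determine which variables to include in a multivariate analysis of variance". It adopts this approach from another trial's protocol, which it cites. The next sentence adds: "Post-hoc multiple comparisons (for example, Bonferroni correction) will be performed to determine where significant differences lie". The general threshold, given beside the efficacy analyses, is "Statistical significance will be considered as *P <*0.05"; it is not tied to the screen.

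The candidate variables are not open-ended. The Background hypothesises "decreased experiential avoidance and cognitive fusion, as well as increased emotional awareness, acceptance and valued living". The section on process measures says that "primary process outcome measures include experiential avoidance, cognitive fusion, acceptance and valued living", and Table 2 assigns these four constructs to five instruments: AFQ-Y, PANAS-X, TAS-20, CAMM-20 and VLQ.

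The population is small: "process outcome measures have been developed for adolescents only", and the Participants section plans 60 adolescents over three arms.

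A further analysis is named in the same paragraph: "Mediational analysis, a regression-based approach, will be used to test hypotheses about the mechanisms behind outcome". The text does not say that it depends on the screen.

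**The concern.** A list of hypothesised mechanisms set before the data does not need to be pruned by the data. Pruning it by a test of the same contrast that the MANOVA then tests makes the second test close to a repeat of the first. A process score that already differs between arms at P<0.05 will nearly always give a significant MANOVA, so the multivariate test no longer protects against chance findings across several scores. A Bonferroni step placed after the MANOVA counts only the variables that survived, not all those examined.

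At stake are the P values for group differences on process measures. These would be reported as part of the evidence on how ACT works, which is the trial's declared secondary aim. The efficacy conclusions are not touched.

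**Working it through.** **The plan's own figure.** The article gives no error rate for the mechanism analysis. Its one computed figure, at least 30 participants per group, concerns efficacy and has no bearing here. The benchmark is the nominal 0.05.

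**Inputs from the article.** There are 60 adolescents and three arms, so 60 / 3 = 20 per arm if allocation is equal (an assumption). Table 2 names five instruments.

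**Inputs that are assumed.** The screen uses P<0.05, there is one score per instrument, data are normal, and scores correlate 0 to 0.5 with one another. The article does not state the screening threshold, which groups the t-tests compare, what is correlated with what, or whether a variable must pass one screen or both. Each reading was therefore run separately.

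**Step 1: chance that something passes a t-test screen when nothing differs.** With five independent scores, 1 − 0.95^5 = 1 − 0.774 = 0.226.

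**Step 2: the MANOVA after the screen.** Trials were simulated with no arm difference on any score. The screen was applied, then a MANOVA at 0.05 on the retained scores only; a trial with nothing retained counts as no rejection. The main runs used 2,500 trials per setting, so the Monte Carlo standard error at a rate of 0.20 is √(0.20 × 0.80 / 2500) = 0.008. Further runs extended the correlation between process scores and outcome to 0.5.

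| Reading of the screen (five scores) | MANOVA false-positive rate |
|---|---|
| No screen, all five entered | about 5% |
| ACT v CBT t-test, then two-arm MANOVA | 18% to 23% |
| Any pairwise arm t-test, then three-arm MANOVA | 15% to 23% |
| t-test and correlation both required; scores correlate 0.3 to 0.5 with outcome | 8% to 19% |
| t-test and correlation both required; scores unrelated to outcome | 1% to 2% |
| t-test or correlation suffices | 6% to 19% |
| Correlation with outcome only | 1% to 5% |

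**Step 3: why the rows differ.** In the two-arm row, once any score is retained the MANOVA rejects in 96% to 100% of trials, so its rate is almost the pass rate from step 1. With both screens required, related scores tend to pass the correlation screen and the t-test decides; unrelated scores rarely pass both. With either screen sufficient, related scores mostly enter through the correlation, so the MANOVA approaches the full set and the rate falls towards nominal. Correlation with outcome alone does not select on the arm difference, so it does not inflate the test.

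**Step 4: Bonferroni over the survivors.** With the two-arm t-test screen, at least one false variable-level claim remains in 17% to 22% of null trials. Often only one score survives, so nothing is left to correct for. For comparison, Bonferroni at 0.05 / 5 = 0.01 over all five independent scores gives 1 − 0.99^5 = 0.049.

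**Step 5: what the fix costs in power.** Take 20 v 20, independent scores and a true difference of 0.65 SD on one score only. The non-centrality is (20 × 20 / 40) × 0.65² = 10 × 0.4225 = 4.225. Hotelling's T² then has power 0.52 with one score entered, 0.30 with four and 0.26 with five.

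**The case against.** The strongest reply is that the article does not fix the rule tightly enough to give it an error rate. Contrast, cut-off and the way the screens combine are unstated. They may stand in the full protocol, an analysis plan or the cited trial's protocol, and an article may properly leave them there. This stands as far as size is concerned. A reader might infer that the stated rule as such inflates error several-fold, but the document does not support that: its wording admits readings from below nominal to more than four times nominal (23% against 5%). It does not remove the point itself. Selection on the trial's own data is stated, and a later document that follows the article inherits it.

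Second, mechanism has its own test, the mediation analysis. This also stands. A reader might infer that the rule produces false claims of mechanism. A significant MANOVA shows a group difference on process scores, not mediation, and nothing in the text feeds the screen into the mediation models. The figures apply to group differences only.

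Third, a reader might split the scales into ten sub-scores and arrive at rates of 26% to 42%. The article nowhere says that sub-scores are screened separately; Table 2 names four constructs on five instruments. The five-score case is the supportable one.

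Fourth, retained effects might be thought to be biased upward. Nothing computed here measures that, so it forms no part of the point.

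**Conclusion.** The concern holds in conditional form. The article prescribes data-driven selection of process variables from a set that it has already fixed, and uses the same adolescents for the selection and the test. Where arm t-tests alone gate entry at P<0.05, the MANOVA's false-positive rate for group differences on process measures is about 15% to 23%, and the post-hoc Bonferroni step as placed does not repair it. Under other readings the rate runs from about 1% to 19%.

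The figures rest on about 20 adolescents per arm, five scores, normal data and inter-score correlations of 0 to 0.5. They say nothing about the mediation analysis or the efficacy results. As this is a secondary aim in adolescents only, the point is a worthwhile and cheap correction, not a threat to the trial's main conclusions.

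**What to change.** Delete the step in which correlations and t-tests choose the MANOVA variables. Enter all pre-specified process scores, one per instrument or per hypothesised mechanism, naming the score wherever an instrument yields more than one. Apply Bonferroni or Holm over that full fixed set. Report the correlations and t-tests as descriptive only. When the set is listed, settle whether emotional awareness belongs to it: it is in the Background hypothesis but is not a construct in Table 2.

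The change is one of wording and needs no further participants or data. Its cost is lower MANOVA power with four or five dependent variables and about 20 per arm. In the example worked above, power is 0.30 or 0.26, against 0.52 if only the one truly different score were tested; that score cannot be known in advance.

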**Methods/design:**

We will recruit 150 young people (90 children and 60 adolescents) diagnosed with an anxiety disorder and their parent or caregiver. After completion of baseline assessment, participants will be randomized to one of three conditions (Acceptance and Commitment Therapy, Cognitive Behavior Therapy or waitlist control). Those in the Acceptance and Commitment Therapy and Cognitive Behavior Therapy groups will receive 10 × 1.5 hour weekly group-therapy sessions using a manualized treatment program, in accordance with the relevant therapy, to be delivered by psychologists. Controls will receive the Cognitive Behavior Therapy program after 10 weeks waitlisted. Repeated measures will be taken immediately post-therapy and at three months after therapy cessation.

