### Secondary measures

*Child Depression Inventory (CDI)*[46]*.* The CDI is one of the most widely utilized and cited diagnostic instruments for depression in children [47,48]. It is a 27-item self-report assessment, adapted from the Beck Depression Inventory [48]. Research has found the CDI test-retest reliability to be moderate range for clinical samples and adequate internal consistency, concurrent validity [47] and discriminant validity have been established [46].

*Children’s Anxiety Life Interference Scale - Child Form (CALIS-C)*[49]*- Adolescents only.* The CALIS-C is a 10-item self-report questionnaire about the impact of fears and worries on an adolescent’s quality of life, self-efficacy and well-being [49]. Reliability estimates were found to be adequate; moderate-to-strong convergent validity and discriminant validity have been observed [49]. The CALIS-C also demonstrates sensitivity to change [49].

*McMaster Family Assessment Device (FAD)*[50]*.* The FAD is a 53-item inventory completed by caregivers on the structure, organization and patterns of transactions within families [50]. Six dimensions of family functioning are identified in the model including Problem Solving, Communication, Roles, Affective Responsiveness, Affective Involvement and Behavioral Control [50]. Moderate-to-strong reliabilities have been obtained for the FAD [50]. It also has established discriminant [50] and concurrent validity [51].

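### The ROC cut-point for treatment success is derived from the trial's only sample with no optimism correction described, so accuracy read from that sample would be biased upward

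*Protocol article*

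**What the plan says.** All of the procedure is in the Statistical analysis section of the protocol article.

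- The model: "Multivariate regression examining factors related to treatment success will also be employed". The candidate predictors are left open: "any demographic (such as age, gender, family functioning) and clinical (such as pre-scores, psychological flexibility) factors that might be related to outcomes".
- The curve: "Receiver operating curve plots of the true positive and false positive rate for different possible cut-points of the regression test will be conducted". The reason given is that such curves "convey information relating to the trade-off between sensitivity and specificity, and maximize predictive value".
- The cut-point: "The coordinates of the receiver operating curve will be used to determine the optimal cut-point for the test".

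The data available are those of the trial itself: "We will recruit 150 young people (90 children and 60 adolescents) diagnosed with an anxiety disorder". The document mentions no hold-out sample, resampling or external validation for this analysis. It does not name the criterion that makes a cut-point optimal.

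**The concern.** A regression score is fitted to maximise its agreement with the outcomes in the sample at hand. A cut-point read off the resulting ROC curve is then tuned to the same outcomes a second time. Sensitivity, specificity and AUC computed on those participants contain both layers of tuning and overstate what the rule would do in new patients. The overstatement grows with more predictors and fewer participants.

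This model could be in that position. The predictor list has at least five entries and is open-ended. One of them, psychological flexibility, belongs to the process domain, and those measures are collected in adolescents only (Process measures section). At stake is the credibility of any statement that baseline factors identify who does well.

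**Working it through.** **Inputs from the document**

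- Sample: 150 in total, 60 of them adolescents (Abstract, Methods/design; Participants).
- Predictors: five are named as examples (age, gender, family functioning, pre-scores, psychological flexibility). For family functioning, "Six dimensions of family functioning are identified in the model" (Secondary measures). Entering six scores in place of one gives 5 - 1 + 6 = 10. Hence the range 5 to 10.
- The plan states no accuracy, AUC or sample size for this analysis, so there is no figure of its own to reproduce.

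**Assumptions, not in the document**

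- Predictors are independent, normally distributed and unrelated to success.
- The success rate is 50%, varied from 30% to 70%.
- The model is a logistic regression with all predictors entered.
- The cut-point maximises the Youden index, J = sensitivity + specificity - 1.

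**Method**

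For each setting, 1,000 datasets were simulated. In each, the model was fitted, the ROC curve drawn and the cut-point chosen on the same participants. The fitted model and cut-point were then applied to 1,000 new participants. A useless rule has true AUC 0.50 and true J = 0.

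**Results at 50% success (averages)**

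| Participants | Predictors | Apparent AUC | Apparent sensitivity | Apparent specificity | Apparent J | J in new participants |
|---|---|---|---|---|---|---|
| 60 | 5 | 0.66 | 0.66 | 0.67 | 0.33 | 0.00 |
| 60 | 10 | 0.73 | 0.71 | 0.72 | 0.43 | 0.00 |
| 150 | 1 | 0.54 | 0.56 | 0.58 | 0.13 | 0.00 |
| 150 | 5 | 0.60 | 0.60 | 0.61 | 0.21 | 0.00 |
| 150 | 10 | 0.64 | 0.63 | 0.64 | 0.27 | 0.00 |

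Repeating the 5- and 10-predictor settings with 2,000 datasets each moves no average by more than 0.01. Given the stylised assumptions, I would read the 60-participant results no more finely than AUC 0.65 to 0.73 and sensitivity and specificity 0.63 to 0.75. For 150 participants and 5 predictors, the corresponding reading is AUC about 0.60 and sensitivity and specificity 0.57 to 0.64.

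**Sensitivity to the success rate (30% to 70%)**

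- 60 participants, 5 predictors: AUC 0.66 to 0.68, sensitivity 0.66 to 0.70, specificity 0.66 to 0.71.
- 60 participants, 10 predictors: AUC 0.73 to 0.76, sensitivity 0.71 to 0.75, specificity 0.72 to 0.76.
- 150 participants, 5 predictors: AUC 0.60 to 0.61, sensitivity 0.60 to 0.62, specificity 0.61 to 0.63.

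**How often a useless rule looks respectable**

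At 50% success, apparent J reaches 0.3 or more in 64% of datasets with 60 participants and 5 predictors, and in 94% with 10 predictors. With 150 participants and 5 predictors it does so in 5%.

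**The stated rationale**

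Positive predictive value is sens × p / [sens × p + (1 - spec) × (1 - p)], where p is the success rate. The ROC coordinates contain sens and 1 - spec but not p. Picking a point from them therefore does not in general maximise predictive value. Some ROC criteria, such as minimum expected misclassification cost, do bring in p, but the text names no criterion.

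**The case against.** The strongest reply is that validation of a secondary prediction model is commonly left to a statistical analysis plan, and this is a condensed article. Reading a cut-point from an ROC curve is not an error in itself; the error would be an uncorrected accuracy claim, and the document makes none. This stands in part. The article does not say that in-sample accuracy will be reported, so the bias is conditional on that. But the article does set out the derivation in detail, on the only sample it has, and following it as written gives optimistic figures.

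Other limits also stand:

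- **Which regression.** The ROC sentence follows the mediation analysis, which the section also calls regression-based. The treatment-success model is the more natural reading, but it is a reading.
- **Sample size.** Psychological flexibility is not tied to one instrument, and the subset entering the model is not stated. That 60 is the ceiling holds only if an adolescent-only measure is included. A reader might go further and take 40, that is 60 × 2/3, for the two treatment arms. That needs equal allocation and exclusion of the waitlist arm, and the document states neither for this analysis.
- **Use of the cut-point.** A reader might infer that it will be published as a rule for who benefits. The document does not say so. The tailoring remark in the Background concerns mechanisms of action, not a prognostic threshold.
- **Predictive value.** The phrase may be loose wording for predictive performance, and no consequence of it can be shown.
- **Predictor screening.** Screening by correlation and t-tests is stated for the multivariate analysis of variance, not for this regression.

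**Conclusion.** The concern holds in a conditional form. The plan derives a cut-point from a model fitted to its single sample and describes no correction; accuracy taken from that sample would be biased upward. Under the stated assumptions the bias is large enough to mislead at 60 participants with 5 to 10 predictors, and modest at 150 with 5. It would be stronger to say that the cut-point will look useful whatever the predictors are worth. The document does not support that, because with all 150 participants and few predictors the apparent accuracy would hardly impress anyone. The number of predictors, the subset, the success rate and the cut-point criterion are all assumptions here. The analysis belongs to the secondary part of the trial. Allocation, primary outcomes, sample size and the efficacy tests are unaffected.

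**What to change.** In the Statistical analysis section:

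1. State that the model fit and the cut-point choice, and any predictor screening if it is used, will be repeated within each bootstrap sample or cross-validation fold.
2. Report optimism-corrected AUC, sensitivity and specificity with 95% intervals beside the apparent values, and base any predictive statement on the corrected figures.
3. Label the cut-point exploratory.
4. Replace the wording about maximising predictive value with the criterion actually used, for example the Youden index.

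The cost is a resampling script and a few sentences, with no new data and no change to the design. The reported accuracy will be lower.
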